#### Setting and supervision

All intervention sessions will be held at the same location affiliated with the primary care practice. The PT will teach the activities to the participants in a setting similar to a home-based environment, which will be equipped with tables, chairs, couches, and a kitchen including countertop, cabinets/cupboards, and appliances. The PT that will deliver the intervention has been practicing for 3 years and has experience working with older adults in long-term care and community settings. The PT received training on the delivery of the LiFE intervention by reviewing the LiFE Trainer’s Manual [43]. The PT also implemented some of the LiFE activities into her daily routine, which provided personal experiences to share with the participants. Our approach to delivering the intervention is thought to be applicable to PTs, kinesiologists, and health promoters in family health teams or other primary care settings that may deliver the intervention per protocol using the LiFE Trainer’s Manual.

#### Session 1

The PT will meet with the participants individually during session 1. If a participant joins the program with a spouse/partner, family member, caregiver, or friend, both individuals may attend. The PT will review a 7-day daily routine chart with the participant to assess how, when, and where they can embed the LiFE activities into their daily routine [43]. The PT will administer the LiFE assessment tool, which evaluates musculoskeletal injury history and includes a 10-item balance and strength assessment. The PT will demonstrate each activity and record the level at which the participant can perform the activity (levels 0–4) [43]. The LiFE assessment tool will take 30 min to complete.

The PT will provide an overview of the LiFE program and describe the balance and strength training principles [41]. The PT will teach one to two balance and one to two strength activities, and instruct participants on how to document their plans and execution of the activities using an activity planner [43]. Participants will use the activity planner to identify the how, when, and where components for each activity, and establish a plan for embedding the LiFE activities in daily tasks. The PT will review the activity planner with the participants at subsequent sessions to identify successes and challenges with planning and progressing the activities.

The PT will teach participants how to self-monitor exercise participation using a daily calendar-style diary that asks:Did you do any exercise today? If yes, respond to questions 2–4.Did you do the LiFE strength or balance activities today? How many LiFE strength or balance activities did you do?Did you do any other strength or balance exercises today (NOT taught in the LiFE program)?How many minutes of aerobic PA did you do today? On a 0–10 scale (refer to the Borg Rating of Perceived Exertion Scale) [44, 45], how hard was it?

Adherence calendars will be reviewed at subsequent sessions and monthly thereafter. Session 1 will last 60–90 min.

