Randomized controlled trial (RCT) research demonstrates that exercise programs that include challenging balance and muscle strengthening exercises are effective for improving health outcomes and reducing falls [30, 1, 31, 32]. Recent work by Clemson et al. [1] demonstrated that teaching older adults how to integrate exercise into daily life activities over five home-based individual visits (the Lifestyle-integrated Functional Exercise (LiFE) program) was associated with an increase in self-reported PA, a 31 % reduction in the rate of falls, and improvements in balance and ankle strength compared to controls. The LiFE program is unique such that participants learn activities and then plan ways to integrate them into their day rather than perform them as part of a structured exercise program. An example of integrating the LiFE activities into a daily routine consists of doing a tandem walk on the way to the kitchen as a balance challenge [1]. The LiFE program is an alternative to traditional, structured exercise for increased PA and falls prevention with good retention and adherence rates in older adults aged 70 years or older [1, 30]. Therefore, implementing a group-based version of the LiFE program in a family health team practice (seen as a more efficient and realistic use of resources than individual delivery) is proposed as the next step in determining the feasibility and potential effectiveness of this strategy for chronic disease management and falls prevention. The findings from our pilot feasibility study will inform the feasibility of a future multi-center cluster RCT to evaluate the cost-effectiveness, safety, and effectiveness of a group-based version of the LiFE intervention and similar implementation studies of exercise intervention in primary care.

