to evaluate the number of participants we can recruit to participate in the program from a family health team practice over 6 months; the intervention will be considered feasible without modification if we recruit 30 participants over 6 months based on data collected from the family health team’s geriatric screening program.to determine intervention retention rates; the intervention will be considered feasible without modification if 75 % of the sample completes the 6-month follow-up assessments. This criterion is based on the original LiFE study [1] wherein 78 % of participants completed the 6-month follow-up assessments.to determine adherence to the intervention; the intervention will be considered feasible without modification if 50 % of the participants completes balance and strength activities ≥3 days/week over the 6-month study period. Our criteria are based on RCT data in exercise and falls prevention research wherein completion of balance and strength exercise ≥3 days/week was positively associated with PA and falls outcomes [1, 32, 34–36, 28].

Secondary objectives will evaluate the potential effectiveness of the intervention by measuring PA levels, physical performance, and quality of life, and implementation outcomes to inform a larger trial. Secondary outcome measures, such as PA levels measured using accelerometers or challenges recorded in the implementation log, will inform the future evolution of the research or implementation. Description of outcomes, hypotheses, outcome measures, and statistical analyses in the study protocol are shown in Table 2.

**Table 2 Tab2:** Summary of outcomes, hypotheses, outcome measures, and methods of analysis

Outcomes	Hypotheses	Outcome measures	Methods of analysis
Feasibility			
Recruitment	Recruit ≥30 individuals over 6 months	• No. of participants recruited over 6 months	Descriptive statistics and estimates based on 95 % CI
Retention	Retain ≥75 % of our sample	• No. of participants who complete study visit 2	Descriptive statistics and estimates based on 95 % CI
Adherence	≥50 % of participants will complete exercises ≥3 d/week at 6 months	• Proportion of participants that complete exercises ≥3 d/week at 6 months	Descriptive statistics and estimates based on 95 % CI
Change in patient-centered outcome measures			
PA levels	Improvement from baseline to 6-month follow-up	• Moderate-to-vigorous, light, and sedentary activity via accelerometer	Paired *t* test
		• IPAQ	

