### Outcomes

#### Feasibility

##### Recruitment, retention, and adherence

The primary outcomes are related to feasibility, including the number of participants that are recruited (recruitment) and retained (retention), and the number of days/week that the activities are completed (adherence). Recruitment will be defined as the number of participants recruited over 6 months, including participants who do not consent to their data being collected for research purposes. Retention will be defined as the number of participants who complete study visit 2 at 6-month follow-up. Adherence will be defined as the number of days/week that the participant integrates balance and strength activities into daily tasks and will be recorded daily on calendar-style diaries. Adherence will be 100 % if a participant completes balance and strength activities ≥3 days/week.

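### The adherence diary can miss days with only LiFE activity, and it pools balance with strength, so it cannot verify the primary adherence criterion if both types are required

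*Protocol article*

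**What the plan says.** **The instrument.** Under Session 1, the protocol article lists four diary questions. The first is "Did you do any exercise today? If yes, respond to questions 2–4". The second is "Did you do the LiFE strength or balance activities today", followed by "How many LiFE strength or balance activities did you do". There is one yes/no and one count for the two activity types together.

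**The outcome.** Under Recruitment, retention, and adherence, adherence is the number of days per week on which "the participant integrates balance and strength activities into daily tasks and will be recorded daily on calendar-style diaries". It is 100% "if a participant completes balance and strength activities ≥3 days/week".

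**The decision rule.** Objectives and hypotheses calls the intervention feasible without modification if 50% "of the participants completes balance and strength activities ≥3 days/week over the 6-month study period". Table 2 words the same measure more loosely: "Proportion of participants that complete exercises ≥3 d/week at 6 months". The abstract also speaks only of exercises.

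**The nature of the intervention.** The Background says that "participants learn activities and then plan ways to integrate them into their day rather than perform them as part of a structured exercise program".

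**The concern.** There are two separate weaknesses in the diary.

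1. **The gate.** A participant who does only embedded LiFE activity on a given day may not regard it as exercise, answer no to question 1, and never reach question 2. That day is scored as having no LiFE activity. The multiple imputation planned under Statistical analyses would not repair it, because the day holds a recorded no and not a missing value.
2. **And versus or.** The criterion is worded as balance and strength, but the item accepts either. If both types are required, some days or weeks would be counted that should not be.

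The first error lowers recorded adherence. The second, if it applies, raises it, so the net direction is unknown. Adherence feeds the feasibility rule, the Maintenance dimension in Table 1, and the planned comparison of secondary outcomes in adherent and non-adherent participants. Misclassification would reach all three.

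**Working it through.** The plan gives no figure on this point to reproduce. The check compares the wording and then illustrates how far the diary result could move. All rates below are assumptions, because the article gives none.

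**Wording compared**

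| Place | Activity type | Both types needed? |
|---|---|---|
| Session 1, question 2 and its count | strength or balance | no |
| Objectives and hypotheses; adherence definition | balance and strength | not stated; either reading possible |
| Table 2 and abstract | exercises | no |
| PA levels (description of the diary count) | strength and balance | reads as a class of activities |

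No section says that both types must be done on the same day. If both are required, a count of 1 shows that only one type was done, and a count of 2 or more does not reveal the mix. No later scoring rule can recover it from these items.

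**Gate.** Let *d* be the true LiFE days in a week and *g* the probability that question 1 is answered yes on such a day, taken as constant and independent across days. Then P(diary shows at least 3) = P(Bin(*d*, *g*) ≥ 3). For *d* = 3 this is *g*³; for example 0.95³ = 0.857 and 0.70³ = 0.343.

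| True days *d* | *g* = 0.95 | 0.90 | 0.80 | 0.70 |
|---|---|---|---|---|
| 3 | 0.857 | 0.729 | 0.512 | 0.343 |
| 4 | 0.986 | 0.948 | 0.819 | 0.652 |
| 5 | 0.999 | 0.991 | 0.942 | 0.837 |

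The loss is concentrated at the threshold and is small for frequent performers. These are single-week probabilities; the article does not say how weeks are combined. If they were averaged, expected recorded days would be *d* × *g*: 3 × 0.95 = 2.85 and 3 × 0.70 = 2.10, against 5 × 0.95 = 4.75 and 5 × 0.70 = 3.50.

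**And versus or, if both types were required on the same day.** Take a participant with 5 days a week of strength or balance activity, all counted by the diary. Let *q* be the share of those days that include both types. P(at least 3 days with both) = P(Bin(5, *q*) ≥ 3).

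| *q* | 0.30 | 0.50 | 0.70 | 0.90 |
|---|---|---|---|---|
| Probability | 0.163 | 0.500 | 0.837 | 0.991 |

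If the two types always occur together, the two readings agree.

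**Effect on the feasibility rule.** With the planned minimum of 30 participants and a cut at 15, P(Bin(30, *p*) ≥ 15) is 0.903, 0.572 and 0.175 for a recorded adherent proportion *p* of 60%, 50% and 40%. Near the cut, a shift of 10 points in recorded adherence can change the verdict.

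**The case against.** A reader might infer that the diary cannot measure the criterion at all and that the adherence result is uninterpretable. The case against that reading is good.

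- **The phrase may name a class.** Table 2 and the abstract say only exercises, and the PA levels section uses strength and balance for the same diary count. The authors seem to use the two conjunctions interchangeably. On this reading question 2 gives days per week directly and nothing is overcounted.
- **Participants may well call LiFE exercise.** The word is in the programme's name, and pre-pilot participants in Table 7 used it of the activities. That evidence comes from four people, and the feedback questions themselves spoke of an exercise program, so it lessens the worry about the gate without removing it.
- **There are safeguards.** The physical therapist teaches the diary individually, and calendars are reviewed at sessions and then monthly. Completion instructions may also sit in the study guide, which is not shown. Still, a calendar marked no leaves little trace of an omitted LiFE activity.
- **Overlap may be high.** Table 4 has both types taught from session 1, so a low share of days with both is not the obvious assumption.
- **The stakes are limited.** This is a single-arm pilot that reports adherence descriptively with a 95% confidence interval.

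These points defeat the strong reading. They leave standing that the skip instruction, followed as printed, can lose LiFE-only days, and that the criterion and the item differ in wording.

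**Conclusion.** The point holds in a limited form. The printed skip can cause LiFE-only days to be recorded as non-adherent, and the pooled item cannot verify the criterion if both types are required. If balance and strength names a class of activities, the item does count the right days and the and/or part reduces to inconsistent wording.

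The size is unknown. Under the assumed range of 95% to 70% yes answers, the weekly chance of being recorded at or above the threshold is 0.86 to 0.34 for 3 true days and 0.999 to 0.84 for 5. This assumes independent days; a participant who consistently does not regard LiFE as exercise would be recorded at zero. The documents do not support saying that such answers are common, that both types must fall on the same day, or that the result cannot be interpreted.

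Severity is moderate: a primary feasibility criterion is affected, the possible loss lies mainly near its threshold, and the repair is cheap.

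**What to change.** **For remaining diaries:** ask the LiFE item every day, whatever the answer to question 1, with separate tick boxes for balance and for strength.

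**Before data cleaning:** make Objectives and hypotheses, Table 2 and the adherence definition state one criterion that the diary can score. For diaries already collected, that is balance or strength. Where the new boxes exist, report a both-types version as supplementary. Scoring a day only when both boxes are ticked should not become the main rule by default, because the protocol does not state that requirement.

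**In reporting:** note which diary version was used. Separate strata by version are not needed in a sample of about 30.

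**Timing and cost:** Data collection and management says that data collection is ongoing and that cleaning and analysis have not begun, so both changes are still possible. The cost is a reprint, a minor ethics amendment, one extra tick per day, and two diary versions within one small sample. Days already lost to the gate cannot be recovered, so the earlier diaries may understate adherence and the report should say so.

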#### Sessions 2–5

The PT will teach the program in groups of five or fewer. Participants will learn new balance and strength activities and will progress previously taught activities each session and plan how, when, and where to integrate the activities into the daily life activities [43]. By the end of session 5, the PT will have taught participants all of the balance and strength activities. Sessions 2–5 will last 60 min.

The PT will call the participants 1 week and 1 month following completion of session 5 and provide reinforcement and encouragement to perform the activities, discuss strategies to increase PA and progress the activities, and address any successes and challenges related to the intervention. The phone calls will last 15–30 min.

#### Data collection and management

Standard operating procedures, information letter and consent form, scripts, data forms, and checklists for visits and follow-up calls can be found in the Mi-LiFE study guide, version date August 18, 2014. Detailed instructions on data collection, checklists for visits and follow-up calls, and materials for outcome measures are outlined in the Mi-LiFE study guide. All research staff will review the Mi-LiFE study guide prior to the study start date. The research assistant will manage the study and perform the outcome assessments. Research staff will participate in training on recruitment, outcome assessment, and data management. The research assistant and PT will meet weekly to discuss the intervention delivery, and with the principal investigator or other research staff members as needed. A research staff member will enter data into an excel spreadsheet or statistical software database (e.g. Statistical Package for Social Sciences, SPSS Statistics, IBM, New York, USA). A meeting with the study investigators will be held to discuss program implementation as needed. Outcomes will be assessed at baseline (study visit 1) and 6 months (study visit 2). Recruitment, data collection, and intervention sessions for the trial are ongoing, and data cleaning and analysis has not begun.

### Outcomes

#### Feasibility

##### Recruitment, retention, and adherence

The primary outcomes are related to feasibility, including the number of participants that are recruited (recruitment) and retained (retention), and the number of days/week that the activities are completed (adherence). Recruitment will be defined as the number of participants recruited over 6 months, including participants who do not consent to their data being collected for research purposes. Retention will be defined as the number of participants who complete study visit 2 at 6-month follow-up. Adherence will be defined as the number of days/week that the participant integrates balance and strength activities into daily tasks and will be recorded daily on calendar-style diaries. Adherence will be 100 % if a participant completes balance and strength activities ≥3 days/week.

### Change in patient-centered outcome measures

#### PA levels

Participants will wear a commercially available accelerometer (ActiGraph GT3x, ActiGraph, Florida, USA) over the hip for 7 days, during waking hours and removing for bathing or swimming, following study visits 1 and 2. Participants will be asked to record the dates and times they wore the accelerometer on log diaries. The number of minutes spent in four intensity levels of activity (sedentary, light, moderate, and vigorous) will be determined using standard counts/minute-based intensity cut-points. The cut-points that will be applied are <100 for sedentary behaviors, 100–1041 for light activity, and >1042 for moderate-vigorous PA (a commonly used cut-point for older adults) [46–48]. Tri-axial data will be analyzed in 60-s epochs. Non-wear time will be identified and excluded if ≥60 min of continuous zeros [9]. Filters will be applied based on the dates and times the participant reports wearing the accelerometer. Only participants who wear the accelerometer for at least 4 days and at least 10 h/day will be included in analysis.

Participants will complete the IPAQ at study visits 1 and 2 to evaluate changes in self-reported time (e.g., number of sessions in the past 7 days, duration per session) spent in strength training, yoga/Tai Chi/other balance activity, vigorous PA, moderate PA, walking, and sitting/lying down awake [49]. Data from each activity will be summed to provide a total amount of time spent in PA over 7 days. Reliability and validity of the IPAQ has been reported [49]. Participants will also record daily exercise participation (aerobic PA duration and intensity, number of LiFE and non-LiFE strength and balance exercises completed) on diaries throughout the 6-month study.

#### Physical performance

Participants will complete physical performance tests at study visits 1 and 2. The SPPB [50] measures gait speed in a 4-m walk test, balance in side-by-side, semi-tandem and full-tandem positions [51, 52], and leg strength in the Five-Times-Sit-to-Stand test [53, 54]. Each performance test is assigned a categorical score ranging from 0 (inability to complete the test) to 4 (best performance). A summary score ranging from 0 (worst performance) to 12 (best performance) is calculated by summing the scores from the three performance tests.

#### Quality of life

Health-related quality of life will be assessed using the EuroQOL EQ5D-3L questionnaire at study visits 1 and 2. The EuroQOL EQ5D-3L questionnaire [55] asks the participant to indicate the statement that best describes their present health state with respect to mobility, self-care, usual activities, pain/discomfort, and anxiety/depression. A visual analogue scale will be administered separately, and the participant will be asked to indicate on a 0 to 100 scale (0 = worst imaginable health state to 100 = best imaginable health state) where they would rate their present health state in their own opinion. Evidence of construct validity [56] and good test-retest reliability [57] has been demonstrated.

#### Falls

Participants will be instructed to report whether or not a fall occurred by daily entry in calendar-style diaries throughout the entire 6-month study. A fall will be defined as “a slip or a trip where the person loses their balance and part or all of their body lands on the ground, floor, or lower level” [58]. A fall incidence form will be filled out by the research assistant or PT to document type of fall, location, date and time, injuries (if any), actions completed (e.g., medication, treatment, hospitalization, other), and health-care services use (e.g., physician visit, allied health care, home care, etc.).

#### Harms

Participants will be instructed by the research assistant to report adverse events (AE) or injuries (serious or otherwise) by phone or at intervention sessions. Participants will be asked about illnesses or injuries at follow-up phone calls and study visit 2. Intervention side effects (e.g., pain, falls, and injuries) and three types of AEs will represent secondary outcomes.

The three types of AEs include 1) serious adverse events (Health Canada definition—event that results in death, hospitalization, or disability); 2) events linked to intervention; and 3) events leading to study withdrawal or intervention cessation. If potential AEs are reported, an AE reporting form will be completed. If it is a fall, the fall incidence form will be completed first, and that information will be used to complete the AE reporting form. The principal investigator will review the forms. AEs must be reported to the research ethics boards. A two-member committee of researchers and clinicians not directly involved with data collection will review AEs after all participants complete the intervention and at study end. The committee will determine whether the events were due to the intervention and will have access to all data, and will inform on how we might move toward conduct of a larger-scale trial. There will be no stopping guidelines for the trial.

